### Study Instruments

Questionnaires 1 and 2 will be developed in Qualtrics in January 2026, and both will evaluate self-reported sociodemographic characteristics, including age; gender identity; race/ethnicity; sexual orientation; branch of military service; service-connected disability rating; past 6-month housing status, sexual practices, and street drug use; and if ever heard of, willing to take, or has taken HIV pre-exposure prophylaxis, HIV post-exposure prophylaxis, or doxycycline PEP in the past year. These questions will be adapted from the Collecting Demographic Data at Syringe Services Programs guide, Core Questionnaire, internal VA guidance on taking a brief sexual health history, and self-efficacy scale for HIV risk behaviors [23-25]. Questionnaire 1 will include additional questions, including HIVST usage plan, results, and next steps. Added questions will be derived from the Theoretical Framework of Acceptability Questionnaire, which evaluates affective attitude, burden, ethicality, intervention coherence, opportunity costs, perceived effectiveness, and self-efficacy of health care interventions, as well as one item from the Net Promotor Score “How likely is it that you would recommend to a friend or a colleague?”; they will be asked to rate convenience, privacy, satisfaction, reduced stigma, preference over other testing methods, ability to pay for testing, and other recommended self-tests to add to the VMs (eg, chlamydia/gonorrhea self-swabs) [26,27].

A semi-structured qualitative interview guide will be developed. Participants will be asked about prior HIV testing experiences, knowledge of self-testing, experience accessing via VMs, perceived ease of use, motivations for self-testing, concerns, impact of stigma, support needs, and recommendations for other self-test distribution via VMs [28].

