**Conclusions:**

This study will generate practice-ready evidence on the feasibility, acceptability, and early behavioral impacts of VM-dispensed HIVSTs for veterans. By pairing a stigma-responsive delivery channel with pragmatic measures, findings can inform equitable scale-up across VA and community settings, guide comparative evaluations of distribution channels (VMs, mail-to-home, or clinic pick-up), and support privacy-preserving linkage strategies to confirmatory testing, HIV pre-exposure prophylaxis, and treatment. Results will address a critical evidence gap for veteran-focused HIV prevention and provide parameters for multi-site evaluations.

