## Introduction

San Francisco and Alameda Counties, core jurisdictions in the United States Ending the HIV Epidemic initiative, continue to experience concentrated HIV burden among populations served by the San Francisco Veterans Affairs Health Care System (SFVAHCS) [1]. Despite national recommendations for routine and risk-based screening, testing within Veterans Affairs (VA) care centers remains suboptimal, with many veterans never having been tested [2,3]. Addressing this persistent screening gap requires approaches that extend beyond traditional clinic workflows and that better reflect how veterans prefer to seek prevention services.

Multiple barriers impede routine testing in VA and community settings alike. Veterans report concerns about confidentiality and stigma, competing demands during clinical visits, uncertainty about eligibility or need for testing, and logistical hurdles such as travel and wait times [4]. Clinicians cite limited time, competing priorities, and variable comfort initiating testing discussions [5]. Framed through a behavioral lens, these barriers cluster around privacy, autonomy, convenience, and perceived control—constructs linked to testing avoidance and delayed diagnosis.

HIV self-tests (HIVSTs) are a recommended complement to facility-based testing and can mitigate several of these barriers by enabling private, user-directed testing [1,6-11]. Distributing HIVSTs through vending machines (VMs) further increases anonymity and convenience, while leveraging existing low-touch infrastructure. Early experience from non-VA settings suggests VM distribution is feasible and acceptable; however, its utility for veterans, and its implementation within VA facilities and partnered housing sites, have not been evaluated [12-16].

This protocol responds to this gap by describing a mixed-methods evaluation of VM-dispensed HIVSTs within the SFVAHCS and affiliated supportive housing locations. Guided by the Reach, Evaluation, Adoption, Implementation, and Maintenance (RE-AIM) framework, this study will characterize reach, adoption, and implementation at the site level and assess early individual-level behaviors related to test use [17]. By pairing a stigma-responsive delivery channel with pragmatic measures, this work aims to generate actionable evidence for VA and community partners considering VM-enabled HIV screening.

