## Methods

### Study Aims and Objectives

This is a single-arm, mixed-methods pilot implementation evaluation that aims to evaluate the RE-AIM of VM-dispensed HIVSTs among Veterans located in Northern California (Table 1) [17].

**Table 1. T1:** Study aims and hypotheses.

Aim	Description	Hypothesis
Aim 1: Reach	Characterize HIV risk factors among veterans who obtained ≥1 VM^a^-dispensed HIVST^b^.	Among survey respondents, commonly reported HIV risk indicators will include male-to-male sexual contact, condomless sex, and unregulated drug use in the past 6 months.
Aim 2: Effectiveness (early outcomes; not causal)	Describe early, self-reported outcomes after obtaining a VM-dispensed HIVST (eg, intended use, completed use, results, and planned next steps) and the perceived usefulness of embedded HIV resources.	Most participants will report intending to use or having used the HIVST, will report reviewing the included post-test resources, and will report an intention to seek confirmatory testing and/or prevention services (eg, HIV pre-exposure prophylaxis).
Aim 3: Adoption	Identify which VM locations have the highest HIVST dispensing volume and when dispensing occurs (eg, clinic vs supportive housing; weekday vs after hours).	HIVST dispensing will be the highest at locations with higher baseline VM utilization and/or higher concentration of veterans experiencing housing instability (eg, supportive housing sites or outpatient clinics serving veterans experiencing homelessness).
Aim 4: Implementation and Maintenance	Assess implementation outcomes (eg, direct costs) and acceptability/experience of veterans with VM-dispensed HIVST (eg, convenience, privacy, satisfaction, and preference compared with other access points).	Participants will rate the VM delivery method as highly acceptable (eg, convenient, private, and satisfactory) and will describe VM access as a low-barrier, low-stigma option for obtaining HIV testing; dispensing will be feasible to maintain over the pilot period with measurable restocking workflows.

a VM: vending machine.

b HIVST: HIV self-test.

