### Future Directions

Findings from this pilot should inform a multi-site VA evaluation that tests scale-up strategies and the comparative effectiveness of distribution channels (VMs vs mail-to-home vs clinic pick-up) on reach, equity, and care linkage. A pragmatic stepped-wedge or cluster randomized design across VA and supportive housing partners would allow the estimation of system-level effects while accommodating staged implementation. Future work should also examine reductions in stigma, increased autonomy/convenience, and changes in self-testing efficacy among veteran subgroups (eg, women and gender-diverse veterans, those experiencing homelessness, rural vs urban settings, and diverse racial/ethnic groups).

To strengthen downstream outcomes, next-phase studies could embed privacy-preserving navigation options (eg, quick response [QR] codes or links inside HIVSTs that directly connect veterans to follow-up testing and HIV pre-exposure prophylaxis). Future economic evaluations (implementation costs, and budgetary impact) will be vital for sustainability decisions. Implementation research should compare site-level strategies (staff champions, restocking workflows, and accessibility features) and assess maintenance over time (supply chain reliability, vandalism, theft, policy, and contracting steps). Finally, bundling HIVSTs with sexual health resources (pregnancy tests or syphilis self-tests) warrants further testing to evaluate whether integrated harm-reduction VMs increase first-time HIV testing and accelerate linkage to preventive care and treatment.

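### Aim 4 asks about preference among access points, but the only preference topic listed for Questionnaire 1 compares testing methods; the two should be reconciled

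*Protocol article*

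**What the plan says.** **Aim.** In Table 1 (Study Aims and Objectives), Aim 4 covers implementation outcomes and veterans' acceptability and experience of the machine-dispensed kit. The examples given are "convenience, privacy, satisfaction, and preference compared with other access points". The matching hypothesis takes the delivery route as the thing rated: "Participants will rate the VM delivery method as highly acceptable".

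**Instrument.** Study Instruments gives the topics of Questionnaire 1. Its list runs parallel to the Aim 4 list (convenience, privacy, satisfaction, then preference), but the preference entry reads "preference over other testing methods, ability to pay for testing". The section lists topics, not item wording, and says "Questionnaires 1 and 2 will be developed in Qualtrics in January 2026".

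**Interview.** The topics for the semi-structured interview include "experience accessing via VMs, perceived ease of use, motivations for self-testing", along with earlier testing experiences, concerns and stigma.

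**Test and channel.** The Introduction presents self-testing first and then the machine as an added element: "Distributing HIVSTs through vending machines (VMs) further increases anonymity and convenience". Future Directions names the routes by which the kit could be supplied: "distribution channels (VMs vs mail-to-home vs clinic pick-up".

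**The concern.** The access point and the testing method are different comparators. If the item follows the Study Instruments wording, a favourable answer may reflect approval of self-testing as against a test done by staff. It need not say anything about the machine as against mail or clinic collection.

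The machine is the new element here. The Discussion already regards HIV self-tests as accurate and acceptable across settings, and gives machine distribution to veterans as the gap. The abstract's conclusions say the findings can "guide comparative evaluations of distribution channels (VMs, mail-to-home, or clinic pick-up". What is at stake is whether the one planned preference figure can be reported as the access-point preference that Aim 4 promises.

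**Working it through.** **1. The plan's own figure.** The only related statistic is the precision in Sample Size and Precision: 90 surveys, with a 95% half-width of about 10 percentage points near 50%.
- Surveys: 900 × 0.10 = 90.
- Wald half-width: 1.96 × √(0.25/90) = 0.103, or 10.3 points.
- Wilson half-width: 10.1 points.

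Both agree with the article. Rewording an item changes neither the 90 nor the half-width. The question is what the proportion measures, not how precisely it is estimated.

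**2. The two texts side by side.**

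| | Aim 4 (Table 1) | Questionnaire 1 (Study Instruments) |
|---|---|---|
| Shared topics | convenience, privacy, satisfaction | convenience, privacy, satisfaction |
| Preference is against | other access points | other testing methods |

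The shared topics show that the questionnaire list is meant to serve Aim 4. Only the comparator changes.

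**3. Does the article treat these as different things?** Yes. The Introduction says machine distribution adds to what self-testing already offers. Machines, mail and clinic pick-up in Future Directions are all ways of distributing a self-test. On its ordinary meaning, a testing method does not distinguish between them.

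**4. What the listed topic can and cannot tell apart.** Classify respondents by test type and by preferred source of the kit:

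| Respondent | Answer on testing method | Answer on access point |
|---|---|---|
| Prefers self-test, prefers machine | favourable | machine |
| Prefers self-test, prefers another source | favourable | not machine |
| Prefers staff-performed test, would take a kit from the machine if self-testing | unfavourable | machine |
| Prefers staff-performed test, would take a kit elsewhere if self-testing | unfavourable | not machine |

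An item on testing method separates the first two rows from the last two. It gives the same answer for rows 1 and 2, and for rows 3 and 4. The share preferring the machine is rows 1 plus 3, which such an item does not determine. The article gives no data on how respondents divide, so no size of error can be computed.

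**5. Is the comparison made elsewhere?** The remaining Questionnaire 1 topics are ratings, not choices between sources. The interview, planned for up to 15 veterans, covers the experience of using the machine but lists no comparison with other sources. There is no comparison arm, and eligibility requires having taken a kit from a machine. In the survey, stated preference is therefore the only listed route to an access-point comparison.

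**The case against.** The strongest reply is that no questionnaire item is shown. The article condenses instruments that were still to be built, and the phrase may be loose shorthand for access routes. That stands, so the finding is a mismatch between two statements in the text, not a demonstrated fault in a survey question.

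Four stronger readings are tempting, and the document supports none of them.
- **That liking the kit will be reported as liking the machine.** Data Analysis specifies descriptive statistics only. No scoring or interpretation rule says how the answer will be used.
- **That the response options run one way.** Participants are asked to rate the topics. The anchors are not given, and a low rating could register dissent.
- **That approval of the kit alone could satisfy the Aim 4 hypothesis.** The hypothesis names convenience, privacy and satisfaction, not preference, and its rated object is the delivery method. Study Instruments does not say whether those ratings concern the machine or the kit, which is a reason to state it, but not evidence that they concern the kit.
- **That this pilot must itself compare machine, mail and clinic pick-up.** Table 1 does not define access points that way, and the three-way contrast is described as future work.

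The interviews and the other ratings also bear on how acceptable the machine is, so Aim 4 is not left without data. What survives is that none of them is listed as comparing one access point with another.

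**Conclusion.** The mismatch is in the current text. Aim 4 undertakes to describe preference relative to other access points, and the only preference topic listed for the survey is relative to other testing methods. An item worded as listed would not by itself answer that component of the aim.

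The size is small: one descriptive component in a single-arm pilot, with no effect on the sample size, the stated precision, the dispensing data or the Aim 4 hypothesis as written. No numerical bias is claimed, because the document has nothing to base one on. The conclusion assumes that the final item follows the listed wording in its ordinary sense. If the finished questionnaire already names access points, only the article's description needs correcting.

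**What to change.** Bring Study Instruments into line with Table 1.
- **Preference item.** Word it against named access points, for example: *To get this same self-test, which would you choose: vending machine, mail to home, clinic pick-up, other, no preference?*
- **Test type.** Keep self-test versus staff-performed test as a separate item.
- **Ratings.** State that convenience, privacy and satisfaction refer to getting the test from the machine.

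The cost is a slightly longer form, a minor IRB modification, and possibly a less favourable preference figure. The new item would still be put only to veterans who had already used a machine, so the result should be described as preference among machine users.

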### Veteran Advocates

We will use participatory action research methodology and recruit 4 veteran advocates with lived/living expertise of HIV who reside in California to provide feedback and recommendations on study materials and assist with interpretation and dissemination of study findings [29-31]. Veterans will provide feedback and recommendations on study recruitment materials, education handouts, and instruments (Questionnaires 1 and 2 and the qualitative interview guide) via a feedback form and a virtual focus group (Multimedia Appendix 1). Feedback will be incorporated prior to resource utilization. Each veteran advocate will receive a US $1000 honorarium for their time and expertise (about 5 hours of work).

### Study Administration and Participant Reimbursement

Veterans who dispensed a HIVST via VMs may anonymously complete Questionnaire 1 via web-based link located on the HIVST. Participants will receive a US $20 electronic gift card after completion (maximum of US $40 per participant). Reimbursement will be available for a total of 90 completed questionnaires.

Veterans (n=15) will meet with the research team members for approximately 1 hour to complete an in-person semi-structured qualitative interview. Veterans will need to complete Questionnaire 2 via an iPad, and those who did so would receive a US $100 gift card. Veterans may complete Questionnaire 1 and/or the semi-structured qualitative interview visit (both are not required).

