### Study Measures and Outcomes

Study measures and outcomes will be mapped onto the RE-AIM framework for evaluating individual and organizational factors that determine public health impacts of a program or policy (Table 2) [17].

**Table 2. T2:** Application of the RE-AIM^a^ framework to the proposed study.

Dimensions	Measures/Outcomes	Data source	Data level
Reach the target population	Number of participants who access ≥1 HIVST^b^	HRVM software (EMS, VendNovation LLC)	Organizational
	Participant demographics and characteristics, sexual partners and practices, drug use practices	Electronic Questionnaires 1 and 2	Individual
Effectiveness or efficacy	Participant HIVST usage plan, results, and steps after testing	Electronic Questionnaire 1	Individual
Adoption by target staff, settings, systems, and communities	Number of HIVSTs dispensed, location, date, and time	HRVM software (EMS, VendNovation LLC)	Organizational
Implementation consistency, costs, and adaptations made during delivery	Direct costs (vending machine coils and HIVSTs)	Purchase order invoices	Organizational
Maintenance/sustainment of intervention effects in individuals and settings over time	Participant reported outcome measures	Electronic Questionnaire 1; semi-structured qualitative interview	Individual

a RE-AIM: Reach, Evaluation, Adoption, Implementation, and Maintenance.

b HIVST: HIV self-test.

The RE-AIM framework has been utilized in similar studies evaluating health care provider views on HIVSTs, workplace HIV testing, integrating HIV prevention services into family planning, barriers and facilitators to HIV pre-exposure prophylaxis uptake, and provision of conditional financial incentives to people living with HIV [18-22].

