### Sample Size and Precision

This pilot implementation evaluation is designed to estimate feasibility and acceptability outcomes rather than to test efficacy. Funding was allocated for the purchase of 900 HIVSTs. Assuming 100% distribution during the data collection period, we estimated a ~10% optional survey response rate based on a similar HIVST distribution study and targeted up to 90 completed surveys [16]. With 90 survey responses, descriptive estimates of key feasibility/acceptability proportions (eg, intended/actual test use, satisfaction, and perceived privacy) will have acceptable precision (eg, for proportions near 50%, an approximate 95% CI half-width of ~10 percentage points). We will conduct up to 15 qualitative interviews, which is expected to be sufficient to achieve thematic saturation for a focused inquiry on acceptability, barriers/facilitators, and implementation experiences.

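### The survey target of 90 counts Questionnaire 1 forms, and one veteran can be paid for two, so the ~10-point precision holds only if all 90 come from different veterans

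*Protocol article*

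**What the plan says.** Under Study Administration and Participant Reimbursement, veterans who took a test "may anonymously complete Questionnaire 1 via web-based link located on the HIVST". Each completion earns a US $20 gift card, with a "maximum of US $40 per participant", and "Reimbursement will be available for a total of 90 completed questionnaires". Ethical Considerations repeats the US $40 maximum and ties it to Questionnaire 1. Questionnaire 2 is paid separately at US $100.

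Under Sample Size and Precision, the target is derived from kits: 900 tests, all assumed distributed, and "we estimated a ~10% optional survey response rate based on a similar HIVST distribution study and targeted up to 90 completed surveys". The precision claim follows: "With 90 survey responses, descriptive estimates of key feasibility/acceptability proportions" are said to have acceptable precision, illustrated as "for proportions near 50%, an approximate 95% CI half-width of ~10 percentage points". The examples given are test use, satisfaction and perceived privacy.

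Aim 1 in Table 1 is to characterise veterans who obtained at least one test. For those Reach characteristics, Table 2 gives the data source as "Electronic Questionnaires 1 and 2". Data Collection and Storage says participants will receive alpha-numeric identifiers and that identifying files will be destroyed on completion.

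**The concern.** The article does not say in words that a veteran may complete Questionnaire 1 twice, but the payment terms leave no other reading. Two payments of US $20 make the US $40 maximum, and Questionnaire 2 lies outside that scheme. The eligibility criteria do not exclude someone who has already responded. The 90 is thus a count of forms, while the precision statement works only if it is a count of people.

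Two things are at stake.

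- **Precision.** Satisfaction, perceived privacy and personal characteristics are attributes of a person. A second form from the same veteran adds little or no new information about them, so an interval computed as if there were 90 independent respondents would be too narrow.
- **Weighting.** If some veterans answer twice and others once, the estimate leans towards those who take several tests. A wider interval does not repair that.

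The remedy depends on timing. Any link between two anonymous forms has to be captured when they are completed; an analysis plan written later cannot create it.

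**Working it through.** **Inputs from the protocol article.** 90 responses, p = 0.5, 95% confidence, stated half-width about 10 points (Sample Size and Precision). US $20 per form, US $40 maximum, 90 paid forms (Study Administration and Participant Reimbursement).

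**Inputs not in the documents (assumptions).** The number of veterans r who answer twice, from 0 to 45, and the within-veteran correlation ρ of the two answers, from 0 to 1.

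**Step 1: reproduce the stated figure.** Half-width = 1.96 × √(p(1−p)/n) = 1.96 × √(0.25/90) = 10.3 points. The Wilson interval gives 10.1. The stated figure is right for 90 independent respondents.

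**Step 2: range of distinct veterans.** US $40 / US $20 = 2 paid forms at most, so 90 paid forms come from at least 90/2 = 45 and at most 90 veterans. With r repeaters there are 90 − r veterans.

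**Step 3: keep all 90 forms and allow for repeats.** The design effect is 1 + ρ × (Σm²/Σm − 1), where m is the number of forms per veteran. Here Σm²/Σm = (4r + 90 − 2r)/90 = 1 + r/45, so the design effect is 1 + ρr/45 and the effective n is 90 divided by it. The last column instead keeps one form per veteran, so n = 90 − r.

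| Repeaters r | Veterans | ρ = 0.25 | ρ = 0.5 | ρ = 0.8 | ρ = 1 | One form per veteran |
|---|---|---|---|---|---|---|
| 0 | 90 | 10.3 | 10.3 | 10.3 | 10.3 | 10.3 |
| 9 | 81 | 10.6 | 10.8 | 11.1 | 11.3 | 10.9 |
| 18 | 72 | 10.8 | 11.3 | 11.9 | 12.2 | 11.5 |
| 30 | 60 | 11.2 | 11.9 | 12.8 | 13.3 | 12.7 |
| 45 | 45 | 11.5 | 12.7 | 13.9 | 14.6 | 14.6 |

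Entries are half-widths in percentage points at p = 0.5. Example: r = 18, ρ = 1 gives a design effect of 1.4, effective n = 90/1.4 = 64.3, and 1.96 × √(0.25/64.3) = 12.2. The upper bound is 1.96 × √(0.25/45) = 14.6. For a proportion of 0.8 the corresponding range, 90 down to 45 veterans, is 8.3 to 11.7 points.

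**Step 4: weighting.** With r = 18, repeaters are 18/72 = 25% of veterans but 36/90 = 40% of forms. The form-based proportion then differs from the veteran-based one by 0.40 − 0.25 = 0.15 times the difference between repeaters and single respondents. An assumed difference of 20 points would shift the estimate by 0.15 × 20 = 3 points. The shift vanishes if nobody repeats or if everybody does.

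**Step 5: Questionnaire 2.** The Methods give separate counts (Questionnaire 1, n=90; Questionnaire 2, n=15) and separate payments. Up to 15 veterans could appear in both sources of the Reach characteristics. They do not enter the 90, so the half-widths above are unaffected.

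**The case against.** The precision statement is conditional and hedged: it speaks of responses, of up to 90, and of an approximate figure, and its arithmetic is correct. The repeat share and correlation are unknown, and 14.6 points requires every respondent to answer twice with identical answers. With 18 repeaters the half-width is 10.8 to 12.2. The study is a single-arm descriptive pilot without a test or go/no-go threshold, so an interval a few points wider changes no stated decision. For per-test outcomes (use, result, next steps), a second form about a second kit is legitimate. De-duplication rules may also sit in a fuller protocol or analysis plan that is not shown. All of this stands, and it lowers the severity. It does not remove the mismatch the article itself creates between a cap on forms and a precision figure that needs distinct people.

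Stronger readings are tempting but are not supported:

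- A reader might infer that repeat forms can never be recognised. The US $40 maximum needs some record of who was paid, consent is obtained, and alpha-numeric identifiers are mentioned. What the article leaves open is how these fit with anonymous completion and whether they reach the analysis file.
- A reader might infer from Table 2 that the two questionnaires are pooled and that this also undermines the precision. Listing two data sources is not a pooling rule, and the two are counted separately.
- Dependence on full distribution of the 900 kits is a separate assumption, which the article states openly.

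**Conclusion.** The concern holds, at moderate severity. The 90 is a number of paid forms that may represent 45 to 90 veterans. The half-width of about 10 points is delivered only with 90 distinct respondents (10.3). Otherwise it lies between 10.3 and 14.6 points at p = 0.5, depending on assumed values for the repeat share and within-person correlation and counting paid forms only. If some but not all veterans repeat and every form is kept, Aim 1 characteristics and attitudes give repeaters double weight relative to single respondents.

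A secondary point follows from Table 2 and from the rule that "Veterans may complete Questionnaire 1 and/or the semi-structured qualitative interview visit (both are not required" ): up to 15 veterans could be described twice among the Reach characteristics. This has no bearing on the 90 or its half-width.

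**What to change.** 1. Say whether the 90 are veterans or forms.
2. Add to Questionnaire 1 a self-generated code, or an item asking whether the respondent has completed this questionnaire before. State how this, the payment record and the alpha-numeric identifiers work alongside anonymous completion, and settle it before identifying files are destroyed.
3. Use the first form per veteran for characteristics and attitudes. Keep both forms only for per-test outcomes, with person-clustered intervals.
4. Restate the precision as about 10 points with 90 distinct veterans and up to about 15 points with 45.
5. Report Questionnaire 2 characteristics separately, or remove veterans who also completed Questionnaire 1; the code or prior-completion item needs to cover both questionnaires for the latter.

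The cost is one extra item, a few sentences of text and a slightly less favourable precision statement. Ethics approval dates from August 2025, so a minor amendment may be needed. The article places questionnaire development in January 2026; forms collected before the item is added could be linked only through whatever payment record exists.
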